## Abstract

**Background:**

Up to 95% of people entering treatment for use of alcohol or other drugs (AOD) smoke tobacco. Smokers receiving treatment for AOD use are interested in quitting and make quit attempts, but relapse is more common and rapid compared with the general population of smokers. New ways to address smoking in this population are needed. Electronic nicotine devices (ENDs) or electronic cigarettes hold significant potential as both cessation aids and harm reduction support. This study focuses on the potential of ENDs to facilitate smoking cessation and to sustain it in the medium term among people in treatment for AOD use. The aim of this trial is to explore the effectiveness, feasibility and acceptability of ENDs for smoking cessation compared with combination nicotine replacement therapy (NRT) for clients after discharge from a smoke-free AOD residential withdrawal service.

**Methods/design:**

The study is a pragmatic randomised controlled trial. In total, 100 participants will be recruited following admission to a smoke-free residential withdrawal service in Melbourne, Australia. Participants will complete a baseline survey and be randomised to either the END group (*n* = 50) or the NRT group (*n* = 50) prior to discharge. Both groups will receive telephone counselling support from quitline. Follow-up measures will be assessed at 6 and 12 weeks following discharge. The primary outcome is continuous abstinence from smoking at 12 weeks post discharge. Secondary outcomes include: 7-day point prevalence from smoking, point prevalence abstinence from all nicotine (including NRT and ENDs), cravings and withdrawal, time to relapse, and treatment adherence (use of NRT, ENDs and quitline).

**Discussion:**

This is the first randomised controlled trial to assess the effectiveness and acceptability of ENDs within a population dependent on AOD, a priority group with very high levels of smoking. The research will test a model of how to incorporate novel smoking cessation support into a period of high treatment receptiveness.

**Trial registration:**

Australian New Zealand Clinical Trial Registry, ACTRN12617000849392. Registered on 8 June 2017.

**Electronic supplementary material:**

The online version of this article (10.1186/s13063-018-2786-1) contains supplementary material, which is available to authorized users.

## Background

In Australia, up to 95% of people entering treatment for use of alcohol or other drugs (AOD) smoke tobacco, which is five times more than for the general adult population [1]. A recent large international systematic review (*n* = 37,364) showed that smoking rates among people in treatment for AOD use (84%) are more than double those for people with similar demographic characteristics in the general population (31%) [2]. As a result, people in treatment for AOD use experience a greater tobacco-related disease burden.

People with a mental illness and substance dependence die 25 years earlier than those without such disorders, and the main causes of death are tobacco-related conditions, including cancer, cerebrovascular diseases and chronic respiratory diseases [3]. In fact, smokers with comorbid substance dependence are more likely to die from tobacco-related causes than from other substance-related causes [4, 5], and quitting smoking is associated with longer-term maintenance of recovery from other addictions [6]. In addition to the health effects of tobacco, smoking causes significant financial stress and social isolation among this already disadvantaged group [7]. Smokers receiving treatment for AOD use are interested in quitting and make quit attempts [8]. The number of quit attempts is high, since sustaining cessation is challenging for people with AOD dependence.

While 85% of quit attempts using standard medication and behavioural support fail in the long term (e.g. 12 months) among the general population of smokers [9], this rate is even higher among smokers with AOD use [10]. High relapse rates in this population may be due to factors related to addiction (e.g. smoking-related cues and triggers), lack of cessation support and high levels of smoking in their social network [1, 11]. Three large trials providing AOD clients with traditional behavioural support and nicotine replacement therapy (NRT) achieved short-term (8–12 weeks) abstinence rates between 9% and 33% while in treatment, but most relapsed to smoking following discharge [12–14]. The heavy nicotine dependence among smokers with AOD use is an important contributor to this high relapse rate [8]. NRT is standard practice as a smoking cessation aid for the general population [15] and is recommended in guidelines Australia [16] and other countries [17, 18] for AOD inpatient services. NRT can reduce withdrawal symptoms and cravings and aid cessation. However, our research with AOD users indicates that they are hesitant to use traditional forms of NRT [19]. New ways of thinking about how to address smoking among this population are needed.

### Electronic nicotine devices

Electronic nicotine devices (ENDs) hold significant potential as both cessation aids and harm reduction support. ENDs are a broad range of battery-powered devices that deliver an aerosol of propylene glycol and/or glycerine, nicotine and flavours [20]. Unlike combustible tobacco cigarettes, ENDs deliver nicotine in an inhalable form without burning tobacco. This is an important development, because the vast majority of the health harms of smoking are due to the toxins produced when tobacco is burnt, rather than the nicotine. Like traditional NRT, the provision of nicotine in END vapour reduces cravings and withdrawal symptoms. Furthermore, ENDs also address the behavioural aspects of smoking cigarettes, such as the hand-to-mouth action, and the inhaling and exhaling of “smoke” (vapour) [21]. With practice, users of advanced ENDs can obtain similar blood nicotine levels to cigarette smokers [22]. END aerosol may still contain some toxins, especially if the liquid is overheated, but the number of toxins is much lower than in cigarette smoke and those that are present are at much lower concentrations [23]. A recent extensive review of the scientific evidence on ENDs concluded that they are likely to be around 95% less harmful than cigarettes [23]. Many smokers report using ENDs to help them quit using tobacco cigarettes [24, 25] and smokers with strong intentions to quit are significantly more likely to have used ENDs than smokers with no intention to quit [25]. Further, those who use e-cigarettes daily were significantly more likely to have stopped using cigarettes compared to those who have never tried e-cigarettes [26].

A recent Cochrane review found that ENDs are effective, but not necessarily more effective than other forms of NRT [27]. The authors concluded that this was due to a lack of evidence and recommended more studies be conducted. Trials with smokers in the general population have demonstrated the safety and efficacy of ENDs compared to other forms of NRT. In New Zealand, one study found that verified abstinence rates at 6 months were 7.3% for early-generation low-nicotine-delivery ENDs, 5.8% for NRT patches and 4.1% for placebo ENDs [28]. Cigarette consumption was reduced by at least half in 57% of the participants allocated to nicotine ENDs vs 41% in the patches group and 45% in the placebo group. Median time to relapse was twice that in participants allocated to nicotine ENDs than patches or the placebo. No significant differences in adverse events were observed. A secondary analysis of participants with mental illness found no differences between END and NRT for rates of relapse, but the e-cigarette group had higher levels of smoking reduction, treatment adherence and acceptability [29]. Further, a longitudinal study in the USA found that at the 2-year follow-up, long-term ENDs users had a higher cessation rate (42.4%) than short-term users (14.2%) or non-users (15.6%). Also, for those participants reporting quit attempts, significantly more reported using ENDs as a cessation aid (24.8%) than reported using an FDA-approved NRT (17.8%) [30]. A similar study with people on methadone maintenance therapy found no difference in the effectiveness of e-cigarettes and NRT [29]. Another in people living with mental illness found self-reported combustible tobacco use and breath CO significantly declined among those using an e-cigarette [30]. However, most studies so far have been with small participant numbers or have focused on short-term timeframes. More evidence gathered from well-controlled studies with larger sample sizes to inform policy and practice regarding END use is needed, particularly of the likelihood that alternative forms of nicotine will be taken up as cessation aids or harm reduction tools, and with populations with high smoking prevalence and low quit rates.

## Methods/design

### Aim

The aim of this pilot pragmatic randomised controlled trial is to explore the feasibility, acceptability and effectiveness of providing an END vaping kit with a 12-week supply of liquid nicotine and telephone quitline support compared with a 12-week supply of combination NRT and quitline support to clients upon discharge from a smoke-free AOD residential withdrawal service.

### Design

The study uses a pragmatic design. It is a phase II, open-label, active control, single-centre, exploratory trial of the effectiveness, feasibility and acceptability of ENDs and liquid nicotine plus quitline counselling among AOD clients discharged from care compared to current best practice (combination NRT and quitline counselling) for smoking cessation and relapse prevention. Follow-up measures will be assessed at 6 and 12 weeks after discharge from the service. Due to the nature of the intervention, neither participants nor staff can be blinded to allocation. However, the data safety monitoring committee and the statistician responsible for the data analysis will be blinded. This trial is registered with the Australian New Zealand Clinical Trials Registry (ACTRN12617001205325p). This study has received ethics approval from the Eastern Health human research ethics committee (E16–2016) and the University of Newcastle human research ethics committee (H-2017-0249). The trial follows the recommendations for interventional trials guidelines (SPIRIT; see Additional file 1). The study schedule of enrolment, product supply and assessments is presented in Fig. 1.

**Fig. 1 Fig1:**
[figure not shown]
Schedule of enrolment, product supply and assessments. DUDIT Drug Use Disorders Identification Test, END electronic nicotine device, GP general practitioner, NRT nicotine replacement therapy

### Setting

Participants will be recruited from a 12-bed residential AOD withdrawal service in Melbourne, Australia. The length of stay is 7–10 days, with an average of 8 days. It is staffed by health professionals who provide medical supervision, support, educational and recovery-focused groups, treatment and discharge planning. The site is smoke-free and as part of current usual care, all clients receive NRT while in the programme to assist with the management of their nicotine withdrawal symptoms, but not following discharge.

### Participants

#### Inclusion criteria

Individuals must meet all the following criteria to be enrolled in this study:aged 18 years or overtobacco smoker on entering the residential servicehave the capacity to consent and able to understand the participant materials and follow the study instructions and procedures (e.g. sufficient English language ability)

#### Exclusion criteria

Individuals who meet any the following criteria will not be enrolled in this study:have used an END containing nicotine in the past monthcurrently pregnant or breast-feeding (measured by self-report)currently enrolled in another studyscheduled to be transferred to a long-term rehabilitation unit following discharge from the residential withdrawal unit

### Procedure

During the intake assessment, residential withdrawal unit staff will screen clients for eligibility and notify eligible clients that a research trial is being conducted and ask if they would be interested in receiving more information about the trial from a research assistant (RA) on site. Unit staff will notify the RA which clients are interested in being approached about participating in the project. The RA will approach interested clients 1–6 days post intake, explain the project, provide written participant information sheets and seek written consent. Figure 2 outlines participant recruitment and follow-up.

**Fig. 2 Fig2:**
[figure not shown]
Flow chart of participant recruitment and follow-up. AOD alcohol or other drugs, END electronic nicotine device, NRT nicotine replacement therapy, RA research assistant, Wk week

All potential participants will receive a copy of the participant information and consent form and the project RA will give a full verbal explanation of the trial (aims, procedures, risks and benefits) in lay terms. Potential participants will have the opportunity to discuss the trial and ask questions. Participants will be advised they can withdraw from the study at any time without prejudice and that their decision to participate in the trial or not will in no way affect the care they receive at the residential withdrawal unit. Following this process, the participant will be asked to provide written consent to participate in the study and complete the baseline survey. Consent will also be collected for the research team to use participant contact details at the end of the trial to possibly invite the participant to take part in a one-off telephone interview about their study experience.

After formal enrolment into the trial, participants will be assigned a unique study ID number, which will be in a re-identifiable format. The ID number will be used by the secure online survey platform, into which participants will enter their identifying information (follow-up contact details) and then proceed on to the baseline questionnaire items. The participant-identifying details will be stored separate to other data, while the ID number will be attached to both. Collection of the baseline data will be completed by the participant online via an iPad. At the end of the baseline survey, participants will be randomised 1:1 to an intervention via a computer-sequenced 4–6 block randomisation embedded in the iPad.

Following randomisation, the project RA will notify participants of the intervention group they have been assigned to and take them through the contents of the relevant intervention pack. Both groups will receive:Proactive referral to quitline counselling (call-back service), which provides calls at pre-discharge and on days 1, 3, 7, 14 and 28 post-discharge, with an emphasis on relapse prevention. At least one call will be scheduled during their residential withdrawal stay. The total number and timing of calls will be tailored to client need and smoking status (i.e. with more frequent calls around relapse crises and quit attempts). Participants will be sent a text message prior to being called, since AOD clients are unlikely to pick up calls from a private number. Counsellors will be trained on the use of ENDs, will monitor and encourage correct use of NRT and will work with clients to address barriers to their use.A trial business card that contains the study’s toll-free number

The END group will receive:An information pack that includes printed information on the benefits of quitting (including that quitting tobacco may facilitate AOD reduction) and information about nicotine maintenance, the benefits of vaping instead of smoking and the risks of vaping compared to complete abstinence. The lack of data on th health risks of long-term vaping will be highlighted. Instructions on how to use ENDs and safe storage and handling will be included.A 1-week supply of nicotine patches for use while getting used to the END.An END starter kit. The device (Innokin Endura T22 starter kit) and refill liquid (Nicophar) were selected based on quality assurance and compliance with relevant standards.A 4-week supply of liquid nicotine, with further supplies of liquid nicotine mailed to them twice at 4-week intervals.

The NRT group will receive:An information pack like that provided to the END group, but rather than information on ENDs, it will include instructions on how to use NRT correctly and for how long, plus information on potential side effects (and when to notify a health-care provider), safe storage and handling.Provision of 12 weeks of NRT on the same schedule as for ENDs. They will initially receive a 4-week supply of patches plus a nicotine spray and inhaler, which will be followed by refills including patches plus inhaler, gum and lozenges.

Participants in both groups will be contacted after discharge at 3 weeks and again at 7 weeks to confirm if they would like to receive a second and third supply of the relevant product (for weeks 5–8 and 9–12, respectively).

### Dose modification

For the END group, the dosing schedule of e-liquid provided to participants will be dependent on their nicotine dependence score as measured by the Heaviness of Smoking Index [31, 32]. Participants scoring in the high-nicotine-dependence category will be assigned an initial 4-week e-liquid supply (total 8 × 10 ml bottles) consisting of: 2 × 10 ml bottles of 18 mg e-liquid and 6 × 10 ml bottles of 12 mg e-liquid. This allotment allows for a 1-week supply of 18 mg e-liquid while participants in this group familiarise themselves with the use of the device. The second and third batches of e-liquid will consist of 8 × 10 ml bottles of 12 mg e-liquid only. Participants scoring in the moderate- and low-dependence categories will receive three 4-week supplies of 8 × 10 ml bottles of 12 mg e-liquid.

### Outcomes

#### Primary outcome

The primary outcome is the continuous abstinence from smoking (defined using a modified version of the Russell standard [33]), that is, no more than five (tobacco) cigarettes after their discharge from the residential AOD withdrawal service. Sustained abstinence from discharge will be checked at each follow-up time point, i.e. by self-report at weeks 6 and 12. Sustained abstinence will be assessed from the date of the previous interview: “Since [date] did you smoke at all, even part of a cigarette?” and among those who did: “In the past 6 weeks (that is, since [date]), have you smoked a tobacco cigarette, even a puff?” with the response options: (1) no, not a puff, (2) 1–5 cigarettes or (3) more than five cigarettes.

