### Statistical methods

#### Sample size estimation

We expect to recruit 100 clients over a 10-month period. Approximately 80% of clients to the service are smokers. We will be assuming 50% eligibility and consent into the trial, and 40% attrition at 12 weeks based on our current AOD research. A total of 60 participants at the 12-week follow-up will provide 30 smokers per experimental group. This trial has been designed to provide essential preliminary information for the development of an adequately powered larger superiority trial, including smoking prevalence, response and attrition rates.

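### The primary outcome caps cigarettes at five in total since discharge, but the follow-up item gives banded counts per interval, so an answer of 1–5 at both interviews cannot be classified

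*Protocol article*

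**What the plan says.** The abstract of the protocol article states: "The primary outcome is continuous abstinence from smoking at 12 weeks post discharge". The Primary outcome section gives the criterion, a modified Russell standard: "no more than five (tobacco) cigarettes after their discharge from the residential AOD withdrawal service". Both describe one allowance for the whole period from discharge to week 12.

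The same section sets out the measurement. "Sustained abstinence from discharge will be checked at each follow-up time point, i.e. by self-report at weeks 6 and 12". It then fixes the recall period: "Sustained abstinence will be assessed from the date of the previous interview". Two questions follow. The first asks whether the participant has smoked at all since [date]. The second goes to those who say they have: "In the past 6 weeks (that is, since [date]), have you smoked a tobacco cigarette, even a puff". Its response options are "1) no, not a puff, (2) 1–5 cigarettes or (3) more than five cigarettes".

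The article does not say how the week-6 and week-12 answers are combined.

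**The concern.** The limit is cumulative, but the count restarts at week 6 and is recorded only in bands. Two answers that each look like a pass can add up to a failure, and the bands do not show whether they do. The people concerned lapse occasionally in both halves of follow-up, and they are the ones a five-cigarette allowance exists to sort. This is the primary outcome, and the trial is meant to supply preliminary figures for a larger superiority trial (Sample size estimation; Discussion), so an unclear abstinence rate would be passed on to that design.

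The wording is also unstable when an interview is missed. The counting question equates six weeks with the time since the previous interview, and at week 12 that is true only if week 6 took place.

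**Working it through.** **Inputs.** Threshold: five cigarettes, counted from discharge (Primary outcome). Interviews: weeks 6 and 12. Bands per interview: 0, 1–5, more than 5. Sample: 100 randomised, 50 per arm (abstract). The article's one derived sample-size figure reproduces: 100 × (1 − 0.40) = 60 at week 12, or 30 per group. The point does not depend on it.

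**Step 1: classify every answer pair.** Add the smallest and largest counts that each pair allows and compare the range with five.

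| Week 6 | Week 12 | Total since discharge | Against the limit |
|---|---|---|---|
| 0 | 0 | 0 | met |
| 0 | 1–5 | 1 to 5 | met |
| 1–5 | 0 | 1 to 5 | met |
| 0 | >5 | at least 6 | exceeded |
| >5 | 0 | at least 6 | exceeded |
| 1–5 | >5 | at least 7 | exceeded |
| >5 | 1–5 | at least 7 | exceeded |
| >5 | >5 | at least 12 | exceeded |
| 1–5 | 1–5 | 1+1 = 2 to 5+5 = 10 | **cannot be told** |

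Eight of nine pairs are classifiable and one is not.

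**Step 2: look inside the ambiguous pair.** There are 5 × 5 = 25 whole-number combinations. Ten total five or fewer (4 + 3 + 2 + 1 for week-6 counts of 1, 2, 3, 4) and 15 total six to ten. This counts combinations; it is not a probability. Two illustrative assumptions, with independent counts, show the range:

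- Counts 1 to 5 equally likely: 15/25 = 60% exceed the limit.
- Probability proportional to 1/count: the weights sum to 1 + 1/2 + 1/3 + 1/4 + 1/5 = 2.2833. The products over pairs totalling more than five sum to 1.4636, and 1.4636 / 2.2833² = 28.1% exceed it.

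The document supports neither distribution and does not give the size of the cell.

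**Step 3: look for another item that supplies the count.** Under Secondary outcomes, the point-prevalence item covers only the last 7 days. Cigarettes per day is reported among those who relapse, defined as 7 days of continuous smoking. Time to relapse records when smoking first occurred. The contacts at 3 and 7 weeks (Procedure) are about product supply. None gives a total since discharge.

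**Step 4: take a missed week-6 interview.** The previous interview at week 12 is then the baseline, completed before discharge (Procedure). The first question, asked since that date, still covers the whole period, so a no is correctly abstinent. For a yes, the counting question can be read in two ways. Read as since [date], it covers the whole period and its bands can be compared with five. Read as the past 6 weeks, it covers only the second half. Someone who smoked more than five cigarettes in the first half and none afterwards answers more than five on one reading and not a puff on the other.

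**Step 5: weight of one person.** With all 50 randomised per arm in the denominator (intention to treat), one reclassified participant moves that arm's rate by 1/50 = 2 percentage points.

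**The case against.** A rule for combining two survey answers is commonly left to the full protocol or the analysis plan, and neither is shown. That stands as far as scoring goes: the missing rule is no fault of the article, and a reader may not infer that people who smoked up to ten cigarettes will be scored abstinent. Nothing in the text says that 1–5 twice is a pass. But a later rule can only assign the ambiguous pair to success or failure; it cannot recover a count that was never collected. The article gives the question and its response options explicitly, so the fault lies in the measurement itself.

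Several stronger readings are tempting and do not hold:

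- *The outcome cannot be derived at all.* Eight of nine answer pairs can be.
- *The week-6 window is wrong because it starts at the pre-discharge baseline.* The mismatch is a matter of days in a smoke-free unit (Setting; Procedure). Extra cigarettes there could only push someone over the limit, so it cannot inflate abstinence.
- *Weeks 1 to 6 go unobserved when week 6 is missed.* The first question covers them.
- *Missed week-6 interviews will be common because the plan assumes "40% attrition at 12 weeks based on our current AOD research".* That figure is loss at week 12. The relevant group missed week 6 and came back, and no figure is given for it.
- *The 9% to 33% abstinence cited in the Background gives the expected number of abstainers.* Those rates were reached during treatment in earlier trials, and most participants relapsed after discharge.

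The trial is also described as an exploratory pilot that is not powered for cessation, and no decision is shown to hinge on this cell. That limits the consequences but does not make the item fit the definition.

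**Conclusion.** The concern holds in a limited form. Among participants with both interviews, one answer pattern of nine, 1–5 at week 6 and again at week 12, cannot be classified against the stated limit, because the total may be anything from 2 to 10. Either blanket scoring rule departs from the definition: success lets up to ten cigarettes through, and failure rejects people who smoked 2 to 5. In addition, the counting question contradicts itself at week 12 after a missed week 6, which affects only those who report having smoked. This assumes that [date] is the last interview actually held, as the text states.

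The number affected cannot be computed from the document, so neither the size of the error nor a difference between arms can be claimed. What can be stated is the leverage, 2 percentage points of an arm's rate per person, and the illustrative 28% to 60% of the ambiguous cell exceeding five, which rests wholly on the assumed distributions.

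**What to change.** 1. Anchor the item to the discharge date at both follow-ups, and record the number of tobacco cigarettes smoked since that date.
2. At week 12 the item covers the whole period since discharge, whether or not week 6 was held. The wording that equates this with six weeks is removed.
3. Score abstinence as a total of five or fewer since discharge, and write this rule down.
4. Participants who have had only the banded week-6 interview need no special rule, because the new week-12 item covers them. For those who completed week 12 with the banded item, report the primary rate twice, with 1–5 at both interviews scored as abstinent and as not abstinent. The two results are bounds, and neither should stand alone. Anyone who missed week 6, reported smoking, and answered none or 1–5 on the old counting question belongs in the same bounds.

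The cost is one reworded survey item, one derivation rule and a short ethics notification, with no extra visits or staff. The downside is small: recruitment began on 1 August 2017 (Trial status), so early participants may have banded answers and later ones counts. The form of the item used should be recorded for each participant.
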